**Figure 2. POP Education Module Topics**

[figure not shown]

**Table 3. POP Education Module Flow Summary**

|                   | Section | Time       | Components                                                                                                                                                                                                                                                                                                                                                                                                                                                                  | ADIME                        |
|-------------------|---------|------------|-----------------------------------------------------------------------------------------------------------------------------------------------------------------------------------------------------------------------------------------------------------------------------------------------------------------------------------------------------------------------------------------------------------------------------------------------------------------------------|------------------------------|
| The Little Clinic | Review  | 10 minutes | 
 
▪ Review the DASH Goal Tear Sheet and Goal Tracking Forms†
 
▪ Review Snapshot*
 
▪ Snapshot-guided discussion: 
 
- Feedback from previous goals and action plan
 
- Strengths related to food topic of the week
 
- Weaknesses related to food topic of the week
 
- Barriers to healthy eating
 
 
 
▪ Set DASH goals
 
 | Assessment
†
Diagnosis |

|                         |           |            |                                                                                                                                                                                                                                                                                                                                                                                                                                                                                                                              |                          |
|-------------------------|-----------|------------|------------------------------------------------------------------------------------------------------------------------------------------------------------------------------------------------------------------------------------------------------------------------------------------------------------------------------------------------------------------------------------------------------------------------------------------------------------------------------------------------------------------------------|--------------------------|
| Appropriate POP Setting | Education | 40 minutes | 
 
Orientation to food topic of the week
 
Address learning objectives using at least 2 suggested strategies in each of the following areas of food literacy: selecting DASH compliant foods (e.g. trying something new, reading labels, making substitutions), preparing DASH compliant foods (e.g. recipe identification and modification, meal planning), and discussing the health benefits of DASH.
 
Orientation to POP education strategy-specific tools
 
 | Intervention             |
|                         | Wrap-up   | 10 minutes | 
 
Create action plan for DASH goals
 
Distribute relevant handouts
 
Planning for next visit: 
 
Review/confirm next visit date/time
 
Reminder to complete/return the DASH Goal Tear Sheet and Goal Tracking Forms†
 
 
 
                                                                                                                                                                         | Monitoring
Evaluation |
|                         | Shopping  | 30 minutes | 
 
Participant shops independently
 
                                                                                                                                                                                                                                                                                                                                                                                                                                            |                          |

ADIME; Assessment, Diagnosis, Intervention, Monitoring, and Evaluation: DASH; Dietary Approaches to Stop Hypertension: POP; point-of-purchase.

All visits will be conducted within the same store to which the participant was randomized. Participants will receive a reminder phone call prior to each study visit. All visits will be scheduled within a  $\pm$  3-day window.

24-hr dietary recalls will be scheduled to collect data from 1 weekend day and 2 weekdays.

\*Snapshot refers to a collection of figures and tables highlighting purchase data metrics.

†Handouts to establish targets, goals and action plans, and self-monitoring.

All randomized participants will repeat weight, waist and hip circumference, blood pressure, blood lipid panel, and blood glucose measurements at Day 84. For those randomized to the POP education arms, this will occur at Visit #7.

On Day 84, all randomized participants will be sent an email with a Post-Intervention Survey and Process Evaluation Survey (attached) to be completed within 1 week. Participants will receive a reminder email if these have not completed within 1 week of receiving them. Up to 3 reminder phone calls will be made if these have not completed within 2 weeks of receiving them. After 2 weeks, if a participant still has not filled out the surveys, the study team will call the participant to complete the surveys as soon as possible.

On Day 173, all randomized participants will be sent an email with a subset of the Medical History Survey questions. Participants who were randomized into a POP education arm will also be sent an email 1-3 weeks prior to day 180 inviting them to participate in a focus group. Please see the Focus Group Protocol for more information on the focus group methodology. On Day 180 (the final TLC visit), weight, waist and hip circumference, blood pressure, blood lipid panel, and blood glucose measurements will be repeated in all randomized participants. If a participant has not completed the Medical History Survey questions by Day 180, the participant will be asked to complete them at the visit. Focus groups will take place following Day 180. All randomized participants will be asked for consent to re-contact after Day 180.

**Table 4. Schedule of SuperWIN Procedures**

|                                                            | Days  |           |     |    |    |    |    |    |    |       |         |     |
|------------------------------------------------------------|-------|-----------|-----|----|----|----|----|----|----|-------|---------|-----|
|                                                            | ≥ -30 | -30 to -2 | 0   | 14 | 28 | 42 | 56 | 70 | 84 | 85-99 | 166-180 | 180 |
| Contact Method                                      |       |           |     |    |    |    |    |    |    |       |         |     |
| Phone                                                      | X     | X         |     |    |    |    |    |    |    | X     | X       |     |
| Email                                                      |       | X         | (X) |    |    |    |    |    | X  |       | X       |     |
| Visits (Control Arm)                                       |       |           | X   |    |    |    |    |    | X  |       |         | X   |
| Visits (POP Education Arms)                                |       |           | X   | X  | X  | X  | X  | X  | X  |       |         | X   |
| Procedures to be Completed (All Participants)       |       |           |     |    |    |    |    |    |    |       |         |     |
| Obtain Verbal Consent                                      | X     |           |     |    |    |    |    |    |    |       |         |     |
| Screening for Eligibility                                  | X     |           |     |    |    |    |    |    |    |       |         |     |
| Schedule Visit #1                                          | X     |           |     |    |    |    |    |    |    |       |         |     |
| Review Food Amounts Booklet                                |       | X         |     |    |    |    |    |    |    |       |         |     |
| Complete Demographic Survey                                |       | X         |     |    |    |    |    |    |    |       |         |     |
| Complete Medical History Survey                            |       | X         |     |    |    |    |    |    |    |       | X       |     |
| Complete Pre-Intervention Survey                           |       | X         |     |    |    |    |    |    |    |       |         |     |
| Complete 24-hour Dietary Intake Recalls (3 per time-point) |       | X         |     |    |    |    |    |    |    | X     | X       |     |
| Obtain Written Consent                                     |       |           | X   |    |    |    |    |    |    |       |         |     |
| Measure Height                                             |       |           | X   |    |    |    |    |    |    |       |         |     |
| Measure Weight                                             |       |           | X   |    |    |    |    |    | X  |       |         | X   |
| Measure Waist and Hip Circumferences                       |       |           | X   |    |    |    |    |    | X  |       |         | X   |

|                                                                 |  |  |     |   |   |   |   |   |   |   |  |   |
|-----------------------------------------------------------------|--|--|-----|---|---|---|---|---|---|---|--|---|
| Measure Blood Pressure                                          |  |  | X   |   |   |   |   |   | X |   |  | X |
| Measure Blood Lipid Panel                                       |  |  | X   |   |   |   |   |   | X |   |  | X |
| Measure Blood Glucose                                           |  |  | X   |   |   |   |   |   | X |   |  | X |
| Complete 30-minute MNT (including dietary intake recall review) |  |  | X   |   |   |   |   |   |   |   |  |   |
| Complete Final Assessment of Eligibility                        |  |  | X   |   |   |   |   |   |   |   |  |   |
| Complete Visit #1 Checklist                                     |  |  | X   |   |   |   |   |   |   |   |  |   |
| Assign new Kroger Loyalty ID number                             |  |  | X   |   |   |   |   |   |   |   |  |   |
| Randomize to 1 of 3 Arms                                        |  |  | X   |   |   |   |   |   |   |   |  |   |
| Orient to Randomized Arm                                        |  |  | X   |   |   |   |   |   |   |   |  |   |
| Complete Post-Intervention Survey                               |  |  |     |   |   |   |   |   |   | X |  |   |
| Complete Process Evaluation Survey                              |  |  |     |   |   |   |   |   |   | X |  |   |
| Consent for Re-contact                                          |  |  |     |   |   |   |   |   |   |   |  | X |
| Procedures to be Completed (POP Education Arms Only)     |  |  |     |   |   |   |   |   |   |   |  |   |
| Review Videos                                                   |  |  | (X) |   |   |   |   |   |   |   |  |   |
| Complete POP Education Module (including Snapshot review)       |  |  |     | X | X | X | X | X | X |   |  |   |
| Complete POP Checklist                                          |  |  |     | X | X | X | X | X | X |   |  |   |

TLC; Kroger's The Little Clinic: RDN; registered dietitian nutritionist: POP; point-of-purchase: MNT; medical nutrition therapy.

All visits will be conducted within the same store to which the participant was randomized. Review and confirmation of the date/time of the following appointment is confirmed at each visit. Participants will receive a reminder phone call prior to each study visit.

All visits will be scheduled within a  $\pm$  3-day window.

24-hr dietary recalls will be scheduled to collect data from 1 weekend day and 2 weekdays.

(X) email with link to videos will only be sent to the combined online/in-store POP arm.

## **e. Data Collection Tools**

After providing oral consent, each participant will be emailed electronic surveys through REDCap to collect: demographic, medical, and other pre-intervention information (see attached Demographic Survey, Medical History Survey, and Pre-Intervention Survey). Surveys are to be completed within 7 days. At Day 84, all participants will be emailed the Process Evaluation and Post-Intervention Surveys. These will assess participants' satisfaction and experience with the study interventions as well as changes in perceived food literacy concepts (see attached Process Evaluation Survey and Post-Intervention Survey). At Day 173, all participants will be emailed a subset of the Medical History Survey questions to

capture any changes in medical status that occurred during the time of the study.

For each participant, trained interviewers at CCHMC Bionutrition Core will use the Nutrition Data System for Research (NDSR) computer program to collect a total of 9 x 24-hour dietary intake recalls by phone. NDSR employs the USDA automated multiple-pass method in the collection of the dietary recall information. This method prompts participants to recall general information about their intake on the first pass, more specific details about these foods and amounts on the second pass, with a final review of descriptions and amounts on the third pass. This dietary information will be used to calculate a DASH score [11].

Kroger's existing practice is to link all household member purchases together under one Kroger Loyalty number. As the study inclusion criteria require each participant to be an existing Kroger shopper, each participant should be linked to this Kroger Loyalty number before the start of recruitment. During Visit #1, each participant will be given a *new*, individual Kroger Loyalty number. This new number is for the participant's sole usage for the duration of the study (Day 0 to Day 180); all other household members will continue to use the pre-existing number during this period. This study feature will allow separation of the participant's purchases from those of other household members throughout the study. In addition, household purchase data will be pulled into the study database by 84.51°, using patient identifiable information (e.g. name, address) submitted via password-protected communications, from 365 days prior to Day 0. Purchasing data captured from the new Kroger Loyalty number will be used to prepare metrics for the RDNs to review with each participant assigned to the POP education arms during Visits #2-7. These data will be displayed on study-issued tablets via a web-based, interactive, graphic "Snapshot." The intention of the Snapshot is to individualize POP education visits by the use of electronically, automatically collected data. Purchasing data will be analyzed as a secondary study outcome.

The RDN will measure each participant's height, weight, waist and hip circumferences, blood pressure, blood lipid panel, and blood glucose via a finger stick at Visit #1. A blood lipid panel consists of TC, HDL-C, LDL-C and TG. All measurements, except height, will be repeated at Day 84 and Day 180. These data will be entered into REDCap, an electronic case report form (eCRF) platform.

All visits will be guided and documented by the RDN using a Visit #1 Checklist (Table 2) and a POP Checklist (see attached). This information will be entered into REDCap.

#### **f. Statistical Analysis**

A minimum of 250 adults will be randomized into the study. Approximately 100, 100, and 50 participants will be randomized to the in-store POP education arm, the combination online/in-store POP education arm, and the control arm, respectively (see section *Data Analysis and Data Monitoring* for power calculations and testing plan).

NDSR food data will be used to calculate overall diet quality using the DASH score. The DASH score is a modification of the DASH index developed by Gunther et al. [11]. DASH score is a continuous 90-point measure with higher scores equating to higher DASH diet adherence.

Randomization will use stratification to balance important baseline covariates among study groups. These covariates will be age, sex, and household size.

Data will initially be assessed for their distribution (e.g. normality) and the level of missing values. Descriptive statistics will be calculated for each arm. The primary endpoint will be the change from baseline to Day 90 in the DASH score (as assessed by dietary intake recalls). Using hierarchical testing, up to 2 tests will be performed:

- 1) First test: Any POP education arm vs. control arm
- 2) Second test: In-store POP education arm vs. combined online/in-store POP education arm

An intention-to-treat (ITT) analysis will be used for both tests. The “last observation carried forward” approach will be used for missing data. Ascertainment of DASH score at Day 90 for each participant will require completion of at least 1 of 3 dietary intake recalls. Sensitivity analyses may be performed using a “complete case” approach or multiple imputation techniques.

The primary comparisons will use an analysis of covariance (ANCOVA) model. This multivariable model, controlling for the baseline covariates, will have DASH score as the dependent variable with treatment arm as the independent variable. As part of this process, the normality of distribution of DASH scores at both baseline and Day 90 will be assessed. If necessary, transformations (e.g. log) will be used to satisfy the assumptions of the model. The primary treatment group comparisons will be performed using appropriate contrasts of the randomization arm estimates. Statistical testing will only be performed for the second test if  $p < 0.05$  is met for the first test (i.e. hierarchical testing). This will preserve an alpha-error of 0.05.

Using 100 participants for each intervention arm (total = 200) and 50 participants for the control arm, we have 93% power to detect a 5-point difference in change from baseline in the DASH score at Day 90 between any POP education arm and the control arm. This sample size will also provide 97% power to detect a 5-point difference between the in-store and combined online/in-store POP education arms. Power estimates were done at two-sided alpha = 0.05 and assuming equal standard deviations of 9 for the primary endpoint.

All analyses will be conducted according to the statistical analysis plan (SAP). Exploratory analyses will be done for important subgroups (e.g. sex, age, race). The following table provides examples of power to detect a 5-point difference in change from baseline to Day 90 in the DASH score between the in-store and combined online/in-store POP arms for subgroups. Numerous exploratory analyses will be performed for secondary outcomes, such as dietary quality measured by the Healthy Eating Index-2015 (HEI-2015).

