**Table 5. Statistical Power for Exploratory Subgroup Analyses**

| Subgroup sample size in each treatment group | Power to detect 5-point difference between in store and combination online/in-store POP arms* |
|----------------------------------------------|-----------------------------------------------------------------------------------------------|
| 52, 52                                       | 80%                                                                                           |
| 60, 40                                       | 77%                                                                                           |
| 40, 40                                       | 69%                                                                                           |
| 50, 30                                       | 66%                                                                                           |
| 30, 30                                       | 56%                                                                                           |

\*Note that secondary analyses should be considered exploratory as the alpha error will not be contained at 0.05.

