### Overall Analysis Approach

Descriptive Statistics. Descriptive statistics will consist of mean and standard deviation (SD) and median and interquartile range (IQR) for variables. Counts and percentages will be used for categorical variables. Unless otherwise determined, descriptive statistics will be produced for all variables and all time-points.

Distributions/Transformations. Residuals from models will be examined for primary and key secondary outcomes for distributional properties, to ensure model assumptions (normality and independence of residuals) are met. If they are not met, data transformation or other analysis methods (e.g. nonparametric) will be used.

Treatment Groups. Subjects were randomly assigned to one of three treatment groups: 1) Control; 2) In-store Point-of-Purchase Education (POP1); and 3) Combined Online and In-store Point-of-Purchase Education (POP2). The designation POP1/POP2 will be used to denote the combining of data from POP1 with POP 2.

Primary Outcome and Comparison: The primary outcome is the DASH score. The primary comparison of interest is the change in DASH score between baseline and the 3-month follow-up.

Key Secondary Outcomes: The main secondary outcomes are BMI, SBP, DBP, non-HDL cholesterol, total cholesterol and triglycerides.

Modeling. The primary comparisons will use a mixed model for repeated measures. This multivariable model, controlling for covariates, will have DASH score as the dependent variable with treatment as the independent variable. The primary treatment group comparisons will be performed using appropriate contrasts of the treatment arm estimates.

Significance Level ( $\alpha$ ) and Tests. For the primary and key secondary endpoints, hierarchical testing will be used, first comparing Control vs. POP1/POP2. If  $p < 0.05$  for that test, then the two intervention groups will be compared (POP1 vs. POP2). This will preserve an alpha-error of 0.05. For all other endpoints, testing will be done at the  $\alpha = 0.05$  significance level, with no multiple comparison adjustments. All tests, unless otherwise noted, will be two-sided.

COVID-19 Impact Analysis. Due to the COVID-19 pandemic occurring during the course of the SuperWIN, we have a COVID-19 impact analysis following regulatory guidance, defined below.

Software. Unless otherwise specified, SAS® 9.4 TS1M5 (SAS, Inc., Cary, NC) software will be used for all analyses.

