# Subgroups of Interest: Primary Endpoint at 3 Mon

| Subgroup                                           | POP1/POP2 | Control | Absolute Mean DASH Difference
(compared to Control) |
|----------------------------------------------------|-----------|---------|--------------------------------------------------------|
| Age
21-50
51-75                              |           |         |                                                        |
| Gender
Male
Female                           |           |         |                                                        |
| Race
White
Not White                         |           |         |                                                        |
| Married
Yes
No                               |           |         |                                                        |
| Education
Bachelor/Graduate
Not              |           |         |                                                        |
| Employment
Fulltime
Not Fulltime             |           |         |                                                        |
| Annual Household Income
≥\$100,000
Less      |           |         |                                                        |
| Household Size
Single Person
More            |           |         |                                                        |
| Frequency of Cooking at Home
≥5-6x/week
Less |           |         |                                                        |
| Activity level
Moderate/very
Less            |           |         |                                                        |
| Hypercholesterolemia
Yes
No                  |           |         |                                                        |
| Hypertension
Yes
No                          |           |         |                                                        |
| Obese                                              |           |         |                                                        |

|                                              |  |  |  |
|----------------------------------------------|--|--|--|
| Yes
No                                    |  |  |  |
| Baseline DASH Score
Above ≥40
Below 40 |  |  |  |

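### The 97% power for in-store versus combined holds only once the first test is passed, and the subgroup power table covers a comparison the SAP subgroup analysis does not make

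*Combined protocol and SAP*

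**What the plan says.** Protocol section 5f orders two tests: the pooled education arms against control, then in-store against combined. On the condition, it says "Statistical testing will only be performed for the second test if" the first test gives p < 0.05. The SAP (Overall Analysis Approach) sets the same order and condition.

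For power, the protocol plans on 100 people in each education group and 50 controls. About the pooled comparison it claims "we have 93% power to detect a 5-point difference in change from baseline in the DASH score at Day 90", and about the second test it adds "This sample size will also provide 97% power to detect a 5-point difference between the in-store and combined online/in-store POP education arms". The inputs are given as follows: "Power estimates were done at two-sided alpha = 0.05 and assuming equal standard deviations of 9 for the primary endpoint". Neither document gives the chance of passing both steps or the gain assumed for each education arm over control. The protocol abstract describes the study as well powered for both questions, without qualification.

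For subgroups, the power column of protocol Table 5 is headed "Power to detect 5-point difference between in store and combination online/in-store POP arms". Its footnote calls these analyses exploratory. The SAP subgroup table (Subgroups of Interest: Primary Endpoint at 3 Mon) has columns for the pooled arms, for control, and for "Absolute Mean DASH Difference" relative to control. It has no column for in-store against combined. Supplementary Table S20 reports the same pooled comparison and adds interaction p-values.

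**The concern.** In a hierarchical procedure, the second comparison can succeed only if the first does. Its power under the plan is therefore the probability of passing both tests. That depends on how far the two education arms together lie above control, as well as on the gap between them. A figure that omits the first step answers a narrower question: how likely is significance if the second test is run?

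At stake is the second research question, whether in-store and combined education differ. If most of the benefit came from the online tools, the pooled effect would be diluted and the test of those tools might not be run.

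The subgroup table raises a related but smaller issue. The power it shows is for a comparison that the SAP subgroup table does not include. The comparison that is included rests on the smallest arm.

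**Working it through.** **Inputs** (protocol section 5f): SD 9 in every arm; two-sided alpha 0.05; 100 in-store, 100 combined, 50 control; 5-point differences. No arm-specific gains over control are given, so those below are assumptions.

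**Step 1: the printed figures.** Power is from the noncentral t with noncentrality d / [9 × √(1/n₁ + 1/n₂)].

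- First test, 200 v 50: SE = 9 × √(1/200 + 1/50) = 1.423; 5/1.423 = 3.51; power 93.8% (printed 93%).
- Second test, 100 v 100: SE = 9 × √(1/100 + 1/100) = 1.273; 5/1.273 = 3.93; power 97.4% (printed 97%).
- Table 5 rows: 80.1, 76.9, 68.9, 66.1 and 56.2% (printed 80, 77, 69, 66 and 56%).

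All reproduce to within a point. The 97% is an ordinary two-sample power that takes no account of the first test.

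**Step 2: both tests together.** The contrasts are (−1, ½, ½) and (0, −1, 1) for control, in-store and combined. Their covariance is proportional to −½/100 + ½/100 = 0. With equal education arms they are uncorrelated, so the joint power is very nearly the product of the two powers. The gap between education arms is 5 points throughout, so the second factor is always 0.974.

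| Assumed gains over control (in-store, combined) | Pooled effect | Power of first test | Joint power |
|---|---|---|---|
| 5, 10 | 7.5 | 0.9995 | 97% |
| 2.5, 7.5 | 5 | 0.938 | 0.938 × 0.974 = 91% |
| 2, 7 | 4.5 | 0.882 | 0.882 × 0.974 = 86% |
| 1.5, 6.5 | 4 | 0.800 | 0.800 × 0.974 = 78% |
| 1, 6 | 3.5 | 0.688 | 0.688 × 0.974 = 67% |
| 0, 5 | 2.5 | 0.417 | 0.417 × 0.974 = 41% |

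The second row uses the protocol's own pooled effect. A simulation of 400,000 trials per scenario with a three-arm pooled SD gave 97.4, 91.4, 86.0, 67.1 and 40.7% for every row except 1.5 and 6.5, which was not simulated. In each, the power given a passed first test stayed at 97.4% to 97.5%.

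**Step 3: the subgroup comparison in the SAP.** This keeps the 5-point effect and SD 9, and assumes control is a quarter of the pooled number within each subgroup (4:1). For the first row, SE = 9 × √(1/104 + 1/26) = 1.973 and 5/1.973 = 2.53.

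| Table 5 row (in-store, combined) | Printed, in-store v combined | Pooled v control | Power |
|---|---|---|---|
| 52, 52 | 80% | 104 v 26 | 71% |
| 60, 40 | 77% | 100 v 25 | 69% |
| 40, 40 | 69% | 80 v 20 | 60% |
| 50, 30 | 66% | 80 v 20 | 60% |
| 30, 30 | 56% | 60 v 15 | 48% |

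The shortfall is 6 to 9 percentage points.

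**Step 4: interaction.** For a factor splitting the trial evenly, each half has 100 pooled and 25 control. The SE of the difference in effects is 9 × √[2 × (1/100 + 1/25)] = 2.846. For a 5-point interaction, 5/2.846 = 1.757, and power is Φ(1.757 − 1.96) = 42%.

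**The case against.** The best defence is that nothing is miscalculated and nothing is hidden. All seven printed powers reproduce, the 93% belongs to the test it describes, and the testing order is set out in the same section as the 97%. The second question can also be read as presupposing some improvement, in which case power given a passed first test is a sensible figure to report. All of this stands, except that the sentence giving the 97% carries no such condition and nor does the abstract.

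Three stronger readings are tempting and should be resisted.

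- A reader might infer that the second question is well powered only if in-store education has a large effect of its own. The table contradicts this: an in-store gain of 2.5 points, half the effect used for sizing, gives 91%, and a gain of 2 points gives 86%.
- A reader might take 41% as the trial's real power for the second test. It is one end of an assumed range, for in-store education with no effect, and nothing in the documents makes that scenario the planning case.
- A reader might conclude that the subgroup plan is seriously misdescribed. The analyses are labelled exploratory, the protocol presents Table 5 as examples, and four of its five rows already show less than 80%. The SAP subgroup table also specifies no interaction test; those p-values appear only in Table S20. The 42% therefore matters only if such tests are meant to be used.

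**Conclusion.** The point holds as one of incomplete power reporting. The 97% is correct for the second test standing alone or once the first is passed, but it is not the power of the procedure that the protocol and SAP prescribe. At the protocol's own 5-point pooled effect, the joint power is about 91%, a loss of about 6 points that still leaves good power. Away from that case the answer depends on unstated arm gains and runs from 97% to 41% over the assumed scenarios. These figures rest on SD 9, a true 5-point gap between the education arms, full planned numbers and equal education arms.

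The subgroup mismatch is real but minor. No printed power applies to the comparison in the SAP subgroup table, and the true figures are 6 to 9 points below the printed ones if the 4:1 ratio holds within subgroups.

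**What to change.** 1. In protocol section 5f, state that 97% is the power of the second test given that the first is passed. Add the joint power, about 91% at a 5-point pooled effect, with the scenario range labelled as assumptions.
2. Qualify the abstract's power claim for the second question in the same terms.
3. Reconcile Table 5 with the SAP by either route: give subgroup power for pooled arms against control, stating the allocation assumed, or add in-store against combined to the SAP subgroup table. If interaction tests like those in Table S20 are intended, specify them in the SAP and give their power.

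The cost is a few sentences and one table, and some figures become less favourable. No extra participants are needed, and the test order and error control are unaffected.
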